#### Recruitment {15}

On average, 70,000 patients visit each participating ED annually, of which approximately 13,000 are current smokers. Each participating hospital will see 20–25 potential participants during “daytime” shifts (7am–7pm) or two per hour. Based on unpublished pilot data gathered from the TOH Civic campus ED in April 2017, 58% of smoking participants who were approached with a “Quit Card” in the waiting area accepted the intervention. Therefore, we estimate that our RC will spend 5 h per day, 5 days per week recruiting participants into both treatment arms of the trial. With approximately 9 smokers every 5 h, we expect that on average 5 smokers per day will be eligible and will consent to participate. Recruitment is expected to take 14 months.

### Assignment of interventions: allocation

#### Sequence generation {16a}

Group allocation will be determined using a random sequence computer generated by a statistical consultant (from the University of Ottawa Heart Institute’s Cardiovascular Research Methods Centre). Randomization will be stratified by two factors: participating site and CTAS level at intake. Two CTAS levels will be used for stratification, the first combining CTAS levels 2 (emergent) and 3 (urgent) and the second combining CTAS levels 4 (less urgent) and 5 (non-urgent).

#### Concealment mechanism {16b}

Prior to recruitment, an equal number of QCI and UC kits will be prepared in opaque packaging, identical in appearance and weight so that the allocation of the next participant will be unpredictable. Kits will be arranged sequentially and kept in two boxes, labeled based on CTAS level.

#### Implementation {16c}

The RC will be responsible for participant enrolment. The RC will approach potential participants strictly based on arrival time to the ED, will assess interest and eligibility, and obtain informed consent. For each new participant, the RC will select the next available kit in the corresponding CTAS level box. Participants will be asked to wait until after the RC has left to open their kits in order to maintain blinding. For those in the QCI group, their Quit Card will need to be registered upon study entry. To maintain RC blinding, each kit (both UC and QCI) will have a sticker on the outside envelope printed with a unique and random card registration number. The RC will enter this number into the Quit Card online portal. Numbers corresponding to true Quit Cards will register the cards, allowing the patient to purchase their NRT. Numbers corresponding to UC kits will be “dummy” codes that when entered into the portal will lead to no further action. Since the RC will not be able to explain the contents of the kits to study participants, both QCI and UC kits will contain simple instructions and contact information for the unblinded research manager if additional questions arise.

### Assignment of interventions: blinding

#### Who will be blinded {17a}

The principal and co-investigators, RC, outcome assessors, and data analysts will be blinded to group assignment for the duration of the study. Data tables incorporating coded group allocations will be presented at specific trial stages to the investigators. Both treatment arms will be grouped according to a specified code, which will not be known to the individuals. Study participants will also be blinded to specific intervention components to reduce performance bias.

#### Procedure for unblinding if needed {17b}

The research manager will receive a password-protected log with each kit number and allocation from the statistical consultant who completed the randomization. In the event of an emergency and/or a situation where the safety, care, and best interest of the participant is compromised by not knowing the treatment allocation, the research manager will initiate unblinding procedures.

### Data collection and management

#### Plans for assessment and collection of outcomes {18a}

The RC will collect baseline data in the ED during recruitment. Blinded research assistants will assess outcomes at week 4 by telephone and weeks 26, 52, and 104 in person. Smoking status will be assessed initially by a self-report of point prevalence abstinence (“Have you used any form of tobacco, even a puff, in the past 7 days?”) and confirmed via expired CO concentration testing using a CO meter. CO levels below 4 ppm will be considered confirmatory of non-smoking [31].

Secondary outcomes related to smoking behavior will be collected by survey and will be gathered in accordance with data-standard guidelines developed by the Ontario Tobacco Research Unit [32]: “How many cigarettes do you smoke per day on the days that you smoke?”; “In the past number of weeks, how many times did you stop smoking for over 24 hours because you were trying to quit?”. To evaluate health services outcomes, participant data will be individually linked to healthcare administrative databases at IC/ES using a unique Ontario Health Insurance Plan number. Mortality data will be acquired through the Registered Persons Database, ED-use data through the Canadian Institutes of Health Information (CIHI)’s National Ambulatory Care Reporting System, and hospital admissions through CIHI’s Discharge Abstract Database. To assess cost-effectiveness, costs associated with the delivery of both the QCI and UC conditions will be gathered. Cost per quality-adjusted life-year gained will be calculated using HR-QoL, collected with the EuroQol 5-dimension 5-level survey (EQ-5D-5L).

Satisfaction and perceived program barriers and facilitators will be assessed for both patients (at 26 weeks) and providers (at the end of each ED’s recruitment period) by open-ended survey questions asked to participants during the 26-week survey.

#### Plans to promote participant retention and complete follow-up {18b}

Overall, we expect high compliance for this smoking cessation trial. Quit cards are likely to be redeemed for medication. Pilot data found that 71% of patients who received a Quit Card used NRT within the first month. Moreover, we expect that participation in behavioral support programs will be followed through to completion. Data from an RCT of the effectiveness of the Ottawa Model for Smoking Cessation (OMSC) program’s behavioral support program observed call completion rates of 83% at day 3, 87% at day 30, and 87% at day 60 [27].

Participants will be compensated for the completion of each assessment in the trial, including baseline and follow-up questionnaires and CO tests. A $25 gift card will be provided to each participant completing the baseline questionnaire, a $10 gift card for the week 4 telephone survey, and $25 gift cards at each subsequent follow-up (total possible $110). In addition, costs associated with follow-up visits will be reimbursed (e.g., parking, transportation costs).

#### Data management {19}

Data will be managed using REDCap electronic data capture platform, where data are entered into a secure, web-based database that complies with Good Clinical Practices and regulatory requirements. The software includes an audit trail, participant and data entry status tracking, real-time data validation checks, and data extraction functionalities. The primary research team (PI, manager, RC, and assistants) will meet weekly to identify and mitigate any potential problems.

#### Confidentiality {27}

All personal health information identifying potential and enrolled participants collected during the study will be stored in paper files, kept in a locked filing cabinet in a restricted access area of the UOHI, or in encrypted electronic files on encrypted (password-protected; only study staff and the principal investigator will know the password) laptops. Details personally identifying participants, e.g., name, address, email) will not be used in data analyses.

#### Plans for collection, laboratory evaluation, and storage of biological specimens for genetic or molecular analysis in this trial/future use {33}

N/A

### Statistical methods

#### Statistical methods for primary and secondary outcomes {20a}

For our primary analysis of the effect of the intervention on smoking abstinence, we will use binary logistic regression. We will complete unadjusted and adjusted models testing for site-by-treatment interactions and assessing the clinically important predictors of level of nicotine dependence and education.

For our analysis of intervention effect on clinical events, we will use competing-risk regression [33]. Competing-risk regression compares the cumulative incidence of an event (i.e., hospitalization, ED visit) between two groups over a period of time in the presence of a competing risk (i.e., death). The primary independent variable in our models will be group (QCI vs. UC group).

We will also assess the effect of quitting on clinical outcomes, using smoking status as the independent variable in our models. An alpha level of 0.05 and two-tails will be used for all tests of significance and interval estimates will be based on 95% confidence intervals. We will use intention-to-treat principles and the Russell standard (the convention in cessation trials), removing patients who have deceased or become untraceable (e.g., number no longer in service, moved with no forwarding address or number) and assuming that those lost to follow-up (e.g., those who refuse contact) are smoking [34]. We will conduct per-protocol analyses using “engaged” participants (all who used their Quit Card and/or partook in ≥1 behavioral support contact). Analyses will be carried out using statistical software packages SAS (Cary, NC) and SPSS.

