#### Sample size {14}

The primary outcome of smoking abstinence at 26 weeks was used to calculate the sample size (PASS 16.0.2, www.ncss.com). Using logistic regression, with 905 participants assigned in a 1:1 allocation to the two groups, we will have 80% power to detect a clinically important 5% difference in smoking abstinence rates between the QCI and UC groups and >90% power to detect a 10% difference (two-sided test; alpha = 0.05). While we have included features to minimize attrition, we have increased our sample to account for a 25% loss to follow-up [30]; therefore, we intend to recruit 1208 participants to allow for per-protocol analyses.

In our assessment of intervention effect on health services, using a two-sided log-rank test and accounting for the competing risk of death, with 1208 participants we will have >90% power to detect a hazard ratio of 0.63 for all-cause re-hospitalization and 77% power to detect a hazard ratio of 0.82 for visits to the ED over 2 years (25% loss to follow-up; alpha = 0.05). We will have >90% power to detect a hazard ratio of 0.45 for death. This assumes cumulative incidence proportions for hospitalization of 0.45 for the UC group and 0.34 for the QCI group, ED visits of 0.68 for UC and 0.66 for QCI, and death of 0.15 for UC and 0.07 for QCI, based on a trial of hospitalized smokers conducted by our group [6].

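### The primary logistic analysis leaves out the CTAS randomisation stratum and does not say whether the unadjusted or the adjusted model is primary; the effect is small and the repair is wording

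*Protocol article*

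**What the plan says.** All references are to the protocol article.

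- **Design.** Sequence generation {16a}: "Randomization will be stratified by two factors: participating site and CTAS level at intake". It continues: "Two CTAS levels will be used for stratification", one combining levels 2 and 3 and the other levels 4 and 5.
- **Primary analysis.** Statistical methods {20a}: "For our primary analysis of the effect of the intervention on smoking abstinence, we will use binary logistic regression". The next sentence gives the models: "We will complete unadjusted and adjusted models testing for site-by-treatment interactions and assessing the clinically important predictors of level of nicotine dependence and education". The same section adds: "An alpha level of 0.05 and two-tails will be used for all tests of significance".
- **Sample size {14}.** "with 905 participants assigned in a 1:1 allocation to the two groups, we will have 80% power to detect a clinically important 5% difference"; and, for attrition, "we have increased our sample to account for a 25% loss to follow-up [30]; therefore, we intend to recruit 1208 participants".
- **A further adjustment.** Concomitant care {11d} says that other cessation aids or programmes used during follow-up will be controlled for, without saying in which model.

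**The concern.** The article names its model terms, and the list does not match its design. One of the two randomisation factors, CTAS, is in no model. The other, site, is mentioned only as part of an interaction test. The usual rule is to analyse by the factors used to stratify.

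The article also announces two models for one primary hypothesis and does not say which supplies the claim. In logistic regression this matters beyond the p-value. The unadjusted model estimates a marginal odds ratio and the adjusted model a conditional one, and these differ even when the arms are perfectly balanced. Two headline odds ratios and two tests at 0.05 are therefore possible, and the choice between them could be made after the results are seen.

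**Working it through.** **1. The plan's own figure.** For a Wald test of the log odds ratio with one binary covariate and 1:1 allocation:

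N = 2 × (z₀.₉₇₅ + z₀.₈₀)² × [1/(p₁q₁) + 1/(p₂q₂)] / (ln OR)²

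Sample size {14} gives no control rate. Assume 5% vs 10%; the only nearby range in the article, 2.6 to 11.3% for passive approaches, contains 5%.

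- (1.960 + 0.842)² = 7.849
- 1/(0.05 × 0.95) + 1/(0.10 × 0.90) = 21.05 + 11.11 = 32.16
- ln OR = ln(0.1111/0.0526) = 0.747; squared, 0.558
- N = 2 × 7.849 × 32.16 / 0.558 ≈ 904.3, so 905, as stated

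For attrition, 905/0.75 gives 1207 and 906/0.75 = 1208, so the inflation is in order. The 905 is an unadjusted two-group calculation.

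**2. What the choice of model changes.** Simulation with N = 905, four sites × two CTAS strata and permuted blocks of 4; 6,000 trials per setting at 5% vs 10%, and 10,000 under the null at 7.5% in both arms. Assumed: site shares 35/35/20/10%; site odds ratios 1, 1.1, 1.2 and 0.8; CTAS, dependence and education each split 50:50; odds ratio 0.5 for dependence and 1.5 for education. In the last row these are 0.33 and 2.0. The documents give none of these values.

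Power (%):

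| CTAS OR | Unadjusted | Site, dependence, education | Same plus CTAS |
|---|---|---|---|
| 1.0 | 80.7 | 81.5 | 81.7 |
| 1.5 | 80.4 | 80.9 | 81.0 |
| 2.0 | 81.4 | 81.8 | 81.9 |
| 3.0 | 82.0 | 82.3 | 82.8 |
| 2.0, stronger covariates | 81.3 | 82.3 | 82.6 |

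Adding CTAS to the adjusted model gains 0.1 to 0.5 points. Going from unadjusted to fully adjusted gains 0.5 to 1.0 points in the first four rows and 1.3 in the last.

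**3. Standard error and estimand.** At CTAS OR 3.0, across the three models:

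- mean SE of the log odds ratio: 0.270, 0.273, 0.276
- mean log odds ratio: 0.753, 0.766, 0.782, i.e. odds ratios of 2.12, 2.15 and 2.19
- ratio of the two: 2.79, 2.81, 2.83

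The SE rises slightly and the conditional estimate rises slightly more. That is where the small power gain comes from.

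**4. Two tests of one hypothesis.** With rejection rates r₁ and r₂ and a proportion d of trials in which the two models disagree, the chance that at least one rejects is (r₁ + r₂ + d)/2. Under the null, unadjusted vs adjusted without CTAS:

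| CTAS OR | r₁ | r₂ | d | Either rejects |
|---|---|---|---|---|
| 1.0 | 4.85% | 4.90% | 0.97% | 5.36% |
| 1.5 | 4.93% | 5.04% | 1.05% | 5.51% |
| 2.0 | 5.04% | 4.99% | 1.03% | 5.53% |
| 3.0 | 4.96% | 4.95% | 0.89% | 5.40% |
| 2.0, stronger covariates | 4.38% | 4.49% | 1.39% | 5.13% |

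The simulation error of a 5% rate over 10,000 trials is √(0.05 × 0.95/10,000) = 0.2 points. A shorter run (5,000 trials per setting, 8% in both arms) gave 5.2 to 5.7%, consistent with this. At 5% vs 10% the two models disagreed on significance in 2.0 to 3.5% of trials.

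**The case against.** The strongest reply is about scope. This is a condensed article, its analysis plan is not shown, and covariate lists are often settled there. The article never says CTAS will be excluded. It calls logistic regression the primary analysis and then lists models, and nothing says that either may supply the claim. The 905 also reproduces as an unadjusted comparison, which fits the unadjusted model leading. This lowers the weight of the point but does not remove it. The article chose its terms, picked two baseline predictors and omitted a randomisation factor, so a later plan would have to change that text and not only expand it. The sample size calculation hints at a lead model but does not designate one.

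Three stronger readings are tempting, and the documents do not support them.

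- **Omitting CTAS wastes precision.** In this model the SE of the log odds ratio does not fall when CTAS is added. Each model's type I error was 4.9 to 5.1% in the main settings (4.4 to 4.7% with stronger covariates), so there is little sign of a badly overstated SE. The article reports no association between CTAS and abstinence that would support a larger loss.
- **Two tests nearly double the error rate.** Independent tests would give 1 − 0.95² = 9.75%. These two are fitted to the same data and correlate at about 0.99.
- **The treatment effect would refer to one site only.** That needs the interaction to be kept in the effect model with reference-cell coding. The article speaks of testing the interaction and specifies neither.

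**Conclusion.** The point holds as a gap in specification with small numerical consequences. Two facts can be read directly from the text: CTAS stratifies the randomisation but is in no stated model, and two models tested at 0.05 share the primary role with neither designated.

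Under the assumed control rate, covariate effects, site shares and block size, adding CTAS is worth at most 0.5 points of power, and freedom to choose between the two models brings type I error to about 5.5%. If both tests held exactly 5%, the stronger-covariate setting would give (5 + 5 + 1.39)/2 = 5.7%. The two odds ratios differ little (2.12 vs 2.15 to 2.19 in the example).

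The case for change rests on a uniquely defined test and estimand that follow the design. It does not rest on efficiency. It is worth making because it is free.

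**What to change.** Revise Statistical methods {20a}, or fix the following in the analysis plan:

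1. One primary model: logistic regression with group, site, CTAS stratum (2-3 vs 4-5), baseline nicotine dependence and education, and no interaction term. A closed list also settles that the follow-up use of other aids mentioned in {11d} is not in this model.
2. Keep the analysis population that {20a} defines. Who is removed or counted as smoking is a separate question and should not change through this edit.
3. From that model, report the standardised risk difference with 95% CI beside the odds ratio, because the trial is sized on a 5-point difference.
4. Fit the site-by-treatment test in a separate model, and label it and the unadjusted model supportive.

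The cost is wording. Site and CTAS are known at allocation. The article does not itemise the baseline questionnaire, so confirm that dependence and education are recorded there; their use as predictors and subgroups implies it. Trial status shows recruitment had not begun when the article was written.

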### Objectives {7}

The main objectives of the INITIATE study are to determine whether, compared to usual care, smokers visiting an ED who receive a proactive tobacco treatment intervention initiated with a “Quit Card”:
Will be more likely to quit smoking over the long term (≥6 months);Will have reduced rates of healthcare utilization and death (from 30 days to ≥ 2 years)?

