### Dissemination plans {31a}

The results of this trial will be released to clinicians, researchers, patients, and funding bodies. Assessment of health and healthcare utilization outcomes such as cost-effectiveness ratios and frequency of ED visits will be of particular interest to administrators and funders.

Knowledge will be shared using conventional academic approaches including high-impact peer-reviewed publications, through the OMSC’s annual conference, and via social media. In particular, the findings will be of interest to the >100 OMSC hospitals across Canada that are seeking strategies to assist smokers in the ED and other high-volume areas.

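### ED visits and admissions are analysed as time to one event per patient, although the objective is a lower rate of use, so repeat events do not count and no visit-rate ratio results

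*Protocol article*

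**What the plan says.** - Protocol article, Objectives {7}, second objective: participants in the Quit Card (QCI) arm "Will have reduced rates of healthcare utilization and death", over a horizon from 30 days to at least 2 years.
- Outcomes {12}: ED visits, hospital admissions and mortality at 4, 26, 52 and 104 weeks. The text does not say whether the first event or the number of events is meant.
- Statistical methods {20a}, the only method given for these outcomes: "Competing-risk regression compares the cumulative incidence of an event (i.e., hospitalization, ED visit) between two groups over a period of time", with death as the competing risk.
- Sample size {14}: power is found "using a two-sided log-rank test and accounting for the competing risk of death, with 1208 participants". For the ED it is 77% at a hazard ratio of 0.82, from cumulative incidences of "ED visits of 0.68 for UC and 0.66 for QCI" and "death of 0.15 for UC and 0.07 for QCI".
- Dissemination plans {31a}: "frequency of ED visits will be of particular interest to administrators and funders".

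No count, rate or recurrent-event analysis is described.

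**The concern.** A log-rank test or competing-risk regression on cumulative incidence uses one event per participant. It asks whether a first visit comes less often or later. It does not ask whether the number of visits per person falls. The two questions separate most when most patients have at least one visit, and the plan expects about two-thirds of each arm to have one. A fall in ED use would then sit largely in second and later visits, which this analysis does not see.

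The intervention could therefore reduce total ED use while the planned comparison reports no difference. Hospital administrators would also receive no estimate of visits avoided per person.

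**Working it through.** **1. Does the stated 77% come from a one-event-per-patient calculation?** Inputs are from Sample size {14}. With F the cumulative incidence, the cause-specific hazard over 2 years is F_ED/(F_ED + F_death) × −ln(1 − F_ED − F_death).

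- Usual care (UC): 0.68/0.83 × −ln(0.17) = 1.452
- QCI: 0.66/0.73 × −ln(0.27) = 1.184
- Ratio: 1.184/1.452 = 0.815 (stated: 0.82)

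Take the 25% loss as an exponential hazard, −ln(0.75) = 0.288 over 2 years, with 604 per arm:

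- UC event probability: 1.452/2.060 × (1 − e^−2.060) = 0.615
- QCI event probability: 1.184/1.597 × (1 − e^−1.597) = 0.591
- Events: 604 × (0.615 + 0.591) ≈ 728
- Schoenfeld power at 0.82: Φ(√728/2 × |ln 0.82| − 1.96) = 76.4%. At 0.815 it is 78.6%.

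The stated 77% lies between these, so it is the power of an analysis in which each patient counts once.

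**2. How much ED use falls outside such an analysis?** The documents give no mean or dispersion. Assume Poisson visits with gamma frailty of variance k, calibrated to the plan's 0.68. The mean is m = −ln(0.32) = 1.14 at k = 0, and m = (0.32^−k − 1)/k otherwise: 1.54, 2.13 and 4.38 for k = 0.5, 1 and 2. Assume also a rate ratio of 0.82.

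- k = 0: repeat visits are 1 − 0.68/1.14 ≈ 40% of all visits. Total visits per person fall by 0.18 × 1.14 = 0.205. The first-visit proportion falls from 0.68 to 0.607, that is by 0.073. About 64% of the fall is in repeat visits.
- k = 1: repeat visits are 1 − 0.68/2.13 ≈ 68% of all visits. The total falls by 0.18 × 2.13 = 0.383 and the first-visit proportion by 0.68 − 0.635 = 0.045. About 88% of the fall is in repeat visits.

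**3. Cost in power for ED visits.** Simulation with 604 per arm, rate ratio 0.82, 5% deaths per arm, no loss and two-sided 0.05. The tests are a first-event test and a total-event rate test with robust variance.

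| k | first event | total events | gap |
|---|---|---|---|
| 0 | 77% | 93% | 16 |
| 0.5 | 62% | 87% | 25 |
| 1 | 46% | 80% | 34 |
| 2 | 29% | 64% | 35 |

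Separate simulation runs agree within about 3 points. With 25% exponential loss the pairs are 72% and 89%, 59% and 83%, 44% and 75%, and 27% and 60%. Under equal rates (k = 1 and 2), both tests rejected in the favourable direction in 2.6 to 3.2% of trials (nominal 2.5%).

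**4. Sensitivity to the assumed effect.**

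- On the cumulative-incidence scale, 0.68 against 0.66 gives ln(0.34)/ln(0.32) = 0.947. At a rate ratio of 0.947 the gap is about 3 to 7 points and both tests are weak. At k = 0 and 604 per arm, the closed-form powers are 11.8% and 16.8%.
- Admissions, UC proportion 0.45, rate ratio 0.63, 604 per arm, closed form: 99.9% and 100% at k = 0, 97.8% and 99.9% at k = 1, 88.9% and 99.5% at k = 2. At 453 per arm the gap is about 1 to 6 points for k up to 1 and 19 points at k = 2.

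**5. Do the two usual total-event estimands agree?** Not under the plan's own deaths. At 15% against 7% mortality, rate ratio 0.82 and no loss, power for the mean count per person against the rate per person-time alive was 72% against 93% (k = 0), 57% against 78% (k = 1) and 42% against 62% (k = 2). Longer survival in QCI gives more time to accrue visits, which dilutes the per-person count.

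**The case against.** The word rates may be loose. The article uses it for proportions elsewhere, such as abstinence and enrolment rates, and Objective 2 applies it to death, which happens once. Read that way, the objective, the power basis and the competing-risk regression agree, and time to event with death competing is a standard choice. An analysis plan that is not shown could also add a count model. These points lower the weight of the matter but do not remove it. Frequency of ED visits is hard to read as a first-visit proportion. The protocol also does not leave the method open: it states one and powers it, and that method cannot yield an event rate.

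Three stronger readings are tempting and not supported:

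- A reader might infer that a loss of 25 points or more is established. It is not. It needs a rate ratio of 0.82, borrowed from a first-event hazard ratio, and clustering that the documents do not quantify. The 5% mortality used above also replaces the plan's 0.15 and 0.07.
- A reader might infer that the plan only tests whether a visit ever occurs. The stated log-rank and hazard-ratio basis is a time-to-event comparison.
- A reader might infer that the dissemination section promises a rate ratio or visits avoided. It says only that frequency will interest administrators and funders.

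**Conclusion.** The mismatch stands. The objective and the dissemination plan speak of rates and frequency of use, while the stated analysis and its power count one event per patient. Repeat visits and admissions do not contribute, and no rate ratio or difference in events per person can be obtained. The fault lies in the estimand and in lost power; type I error is not affected.

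The size is conditional. For ED visits at an assumed rate ratio of 0.82, UC first-visit proportion 0.68, 604 per arm and equal 5% mortality, the loss is about 15 to 17 points without clustering and about 25 to 35 points with gamma variance 0.5 to 2. Near 0.947 it is about 3 to 7 points. For admissions at 0.63 it is small unless clustering is strong. These are secondary outcomes, so the change should be made but the trial does not depend on it.

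**What to change.** For ED visits and hospital admissions, prespecify an analysis of total events from the administrative records whose linkage is already planned (National Ambulatory Care Reporting System and Discharge Abstract Database). Report the ratio and the difference in events per person with 95% confidence intervals. Name one estimand, because the two candidates are not interchangeable:

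- the event rate per person-time alive, from a negative binomial or robust-variance model with a person-time offset, reported alongside mortality; or
- the mean cumulative count with death as a terminal event (Ghosh-Lin), noting that it is diluted if QCI lowers mortality as Sample size {14} assumes.

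Keep the competing-risk first-event regression as a companion analysis, and label the utilization power figures in Sample size {14} as applying to first events only. If first events are what is meant, Objectives {7} and Dissemination plans {31a} should say so.

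The cost is wording and some programming, with no new data or patients. Very frequent users gain influence; the robust variance and the retained first-event analysis address this.

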### Eligibility criteria {10}

Participant inclusion criteria are the following:
Current daily smokers (smoke ≥ 5 cigarettes per day)≥ 18 years of age (the age of majority in Ontario)Assigned a Canadian Triage and Acuity Scale (CTAS) level of 2–5 (emergent to non-urgent)Able to read and understand English or FrenchResides in Ontario and eligible for Ontario Health Insurance Plan (to permit linkage with administrative data housed at the Institute for Clinical Evaluative Sciences [ICES])Available and willing to participate in follow-up assessments over the next 24 monthsHas access to a telephone or computerAble to provide informed consent.

Exclusion criteria are the following:
Currently participating in this or another smoking cessation studyAssigned a CTAS level of 1 (resuscitation—the most seriously ill patients with the highest likelihood of hospital admission) or in a psychiatric emergency unitPregnant, planning to become pregnant over the next 2 years, or breastfeedingHas morbid illness which will prevent completion of 26-week follow-up (e.g., receiving palliative care)In the ED physician’s opinion, manifests acute physical and/or psychiatric illness or has a cognitive impairment that would preclude participation in/benefit from the intervention.

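### The analysis of quitting puts a post-baseline exposure into models built for randomised group, without fixing when quitting is defined or when the event clock starts

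*Protocol article*

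**What the plan says.** All references are to the Protocol article.

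- Eligibility criteria {10} admit only daily smokers: "Current daily smokers (smoke ≥ 5 cigarettes per day".
- Assessment of outcomes {18a} gives the times at which status is learned: "Blinded research assistants will assess outcomes at week 4 by telephone and weeks 26, 52, and 104 in person". Status is self-reported and then checked by expired CO. The primary outcome is CO-verified abstinence at 26 weeks.
- Objectives {7} set the health-services window: "Will have reduced rates of healthcare utilization and death (from 30 days to ≥ 2 years". The secondary outcomes list ED visits, admissions and mortality at 4, 26, 52 and 104 weeks.
- Statistical methods {20a} name the model: "For our analysis of intervention effect on clinical events, we will use competing-risk regression". Its main independent variable is randomised group. The section then adds: "We will also assess the effect of quitting on clinical outcomes, using smoking status as the independent variable in our models".
- The same section removes participants who have died or cannot be traced and treats other losses to follow-up as smokers. It gives no separate rule for the quitting models.

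**The concern.** Randomised group is known at entry, so a clock that starts at entry suits it. Quitting is not known at entry. If later smoking status replaces group in the same models, events that came first are attributed to an exposure measured afterwards.

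Those events can also help to decide the exposure. A participant admitted to hospital in the first months may miss the follow-up visit and be coded as smoking. Another may stop smoking because of the admission. Either route produces an association when quitting has no effect.

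The plan calls the result an effect of quitting. That is a causal label for a contrast that is not randomised and for which no adjustment is described.

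**Working it through.** **1. Inputs.** Sample size {14} gives two-year cumulative incidences: "This assumes cumulative incidence proportions for hospitalization of 0.45 for the UC group and 0.34 for the QCI group", and "ED visits of 0.68 for UC and 0.66 for QCI, and death of 0.15 for UC and 0.07 for QCI". Planned recruitment is 1208, or 604 per arm.

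**2. The plan's own figure.** The section states: "with 1208 participants we will have >90% power to detect a hazard ratio of 0.63 for all-cause re-hospitalization". Expected first hospitalisations are 604 × (0.45 + 0.34) = 477. Schoenfeld power is Φ(√(477/4) × |ln 0.63| − 1.96) = Φ(3.09) = 0.999. After 25% loss (906 participants, 358 events) it is 0.992. The claim reproduces. The stated hazard ratio and incidences do not match exactly under proportional hazards (ln 0.66 / ln 0.55 = 0.70), but only the incidences are used below.

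**3. Share of two-year first events before status is known.** With a constant hazard (an assumption), the proportion with an event by week t is 1 − (1 − p)^(t/104). Both arms are pooled, because this analysis would use both. At week 26:

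- Hospitalisation: UC 1 − 0.55^0.25 = 0.139; QCI 1 − 0.66^0.25 = 0.099. Share = 0.2375/0.79 = 30%, about 143 of 477.
- ED visit: 0.248 + 0.236 = 0.484. Share = 0.484/1.34 = 36%, about 293 of 809.
- Death: 0.040 + 0.018 = 0.058. Share = 0.058/0.22 = 26%, about 35 of 133.

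| Status taken at | Hospitalisation | ED visit | Death |
|---|---|---|---|
| Week 4 | 5% | 6% | 4% |
| Week 26 | 30% | 36% | 26% |
| Week 52 | 57% | 64% | 52% |
| Week 104 | 100% | 100% | 100% |

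If events cluster early (Weibull shape 0.8, also an assumption), the week-26 shares become 39%, 46% and 35%.

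**4. Bias when quitting does nothing.** Take the pooled two-year hospitalisation incidence, (0.45 + 0.34)/2 = 0.395. The weekly hazard is −ln(0.605)/104 = 0.00483. Per participant:

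- first events by week 26: 0.118
- first events in weeks 26-104: 0.277
- person-weeks to first event or week 104: 1.50 from those with an early event and 80.24 from the rest.

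Let q₁ be the probability of being recorded as a quitter after an early event, and q₀ the probability otherwise. The rate ratio, quitters to others, is

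[(0.118q₁ + 0.277q₀)/(1.50q₁ + 80.24q₀)] ÷ [(0.118(1−q₁) + 0.277(1−q₀))/(1.50(1−q₁) + 80.24(1−q₀))].

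*Missed visits coded as smoking.* Assume 10% quit, 80% attend in general, and 50%, 60% or 70% attend after an early admission. Then q₀ = 0.08 and q₁ = 0.05, 0.06 or 0.07. For 50% attendance the two rates are 0.00432 and 0.00488, a ratio of 0.89. For 60% and 70% the ratios are 0.92 and 0.96.

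*Illness prompts quitting.* Assume q₀ = 0.10 and an odds ratio of 1.5 or 2 for quitting after an early admission, so q₁ = 0.143 or 0.182. The ratios are 1.13 and 1.26.

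*Landmark at week 26.* Among those event-free at week 26, both groups have the same later hazard, so the ratio is 1.0 under either mechanism.

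The quitting, attendance and odds-ratio values are illustrative; the protocol gives none of them.

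**The case against.** The strongest reply is that this is one sentence on a secondary analysis in a condensed article, and that the full protocol or SAP may name the assessment and time origin. That limits the weight of the point. It does not remove it, because the sentence already commits to an exposure, a model family and a causal label, and those do not fit together if the sentence is followed as written with 26-week status.

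Several stronger readings are tempting but not supported:

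- *That the plan counts these events from entry.* It does not say so. This is inferred from the reuse of the models built for randomised group.
- *That a third or more of events precede the exposure.* Under constant hazards only ED visits pass a third at week 26, and with week-4 status the share is 4-6%. Higher week-26 figures for usual care, 34% for hospitalisation and 43% for ED visits, arise only if every death is assumed to occur without a prior event, which the documents do not say.
- *That immortal time would create a large survival benefit, with a death hazard ratio near 0.72.* That requires early deaths to be kept and coded as smokers. The plan removes participants who have died; with early deaths removed, the null ratio is about 1.0. The 26% for death is then the share dropped, not events wrongly attributed.
- *That the analysis would favour quitting.* The direction depends on which mechanism dominates.

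The size should also be kept in proportion. With 10% quitting and 477 events, the standard error of the log hazard ratio is about 1/√(477 × 0.1 × 0.9) = 0.15. The attendance mechanism shifts the log ratio by 0.04-0.12, which is less than one standard error. The illness mechanism shifts it by 0.13-0.23.

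**Conclusion.** The point stands as a cheap improvement to a secondary analysis. It is firm that quitting is a post-baseline exposure and that the text gives no defining assessment, time origin, landmark or time-updating. The week-26 shares of 26-36% rest on three conditions: 26-week status, events counted from entry, and constant hazards. The bias is real in mechanism, moderate in size under the assumed inputs, and of unpredictable sign. Removing the dead does not cure it for hospitalisation or ED visits, because participants with early non-fatal events remain in the analysis. The randomised comparisons, the stated objectives and the primary outcome are untouched.

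**What to change.** State in {20a} or in the SAP, before outcome data are seen:

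1. Quitting is defined by the 26-week assessment.
2. The clock starts at that assessment, among participants then alive and, for first-event models, event-free; events are counted from week 26 to week 104. Alternatively, smoking status enters as a time-updated covariate. With that alternative a cause-specific hazard model is simpler, because status is undefined after a competing death.
3. The models adjust for baseline prognostic variables that the plan already uses, such as nicotine dependence and education.
4. The result is reported as an observational association, not as an effect of quitting.

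Fixing the assessment in advance also prevents a later choice among four candidate time points.

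The cost is a few sentences and some precision. Under the assumptions above and before losses, first hospitalisations fall from 477 to about 334 and first ED visits from 809 to about 516. Intervals on the log scale widen by about 20% (√(477/334) = 1.20) and 25% (√(809/516) = 1.25). Deaths fall from 133 to about 98, a reduction that the plan's removal of deceased participants would already bring if it applies here.
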